#### Causal Event Definitions for Serious Adverse Event Reporting

A Serious Adverse Event (SAE) will be reported in accordance with NHMRC and TGA guidelines. For this purpose, the causal event must also be classified as follows:

- 1) Causal event is highly probable if a time relationship exists, no other causative factor(s) exists, there is improvement on dose reduction or dechallenge and reoccurrence on rechallenge has occurred (if performed) or if a specific laboratory test has confirmed the relationship.
- 2) Causal event is probable if a time relationship exists, the event is more likely explained by the study drug than other cause or there is improvement on dechallenge or dose reduction.
- 3) Causal event is possible if a time relationship exists but other possible causative factor may exist. There may or may not be improvement on dechallenge or dose reduction.
- 4) Causal relationship is unlikely if time relationship is non-existent or doubtful and /or other factor(s) are certain or probable to have been causative. Causal relationship in cases where the disease under study has deteriorated due to lack of effect should be classified as unlikely.
- 5) Causal relationship is not related if a time relationship is non-existent or the cause of the event had been identified or the drug cannot be implicated.

## APPENDIX 2

### **APPENDIX 3**

#### **Clinical Frailty Scale**

The Clinical Frailty Scale can be retrieved from:

<https://www.dal.ca/sites/gmr/our-tools/clinical-frailty-scale.html>

## APPENDIX 4

### SLT001 Trial Contingency Measures

In response to the COVID-19 outbreak in Australia, study procedures have been amended to protect the safety and wellbeing of participants, their caregivers as well as the research team, and to minimise the impact of the outbreak on the SLT001 trial. Recruitment is to be paused until the trial centre's public health directive and their governance body allow for recruitment to resume. All active participants and research staff will be managed to prioritise their safety, and these strategies are detailed in this appendix.

#### 1. SLT001 Trial Contingency Measures for New Participants

|     | Activity        | Pre-COVID Status      | Alternate Arrangements                                                                                                                                                                                                                                                                                                                                                                                                                                                                                                                                                                                      | Responsibility | Note/Action                                                                                                                                                                                                                                                                                                                                                                                                                                                                                                                                                       |
|-----|-----------------|-----------------------|-------------------------------------------------------------------------------------------------------------------------------------------------------------------------------------------------------------------------------------------------------------------------------------------------------------------------------------------------------------------------------------------------------------------------------------------------------------------------------------------------------------------------------------------------------------------------------------------------------------|----------------|-------------------------------------------------------------------------------------------------------------------------------------------------------------------------------------------------------------------------------------------------------------------------------------------------------------------------------------------------------------------------------------------------------------------------------------------------------------------------------------------------------------------------------------------------------------------|
| 1.0 | New Recruitment | F2F screening on-site | 
Recruitment is currently suspended.
 
However, recruitment can recommence at centres where the public health directive and their governance body allow for it.
 

COVID-19 safety checks and precautions need to be adhered to until the COVID-19 completely resolves when face-to-face assessments are conducted (see Items 1.1 and 1.2 for more details)

For follow-up visits of the new participants, follow the alternate arrangements outlined in Items 2, 3 and 4 according to the situations and requirements of the relevant site.

 | All Centres    | 
The screening visit must be conducted face-to-face according to current protocol requirements.
 
Actions:
 

Centres to check the local public health directive and their governance body for current advice on recruitment and face-to-face appointments and inform the Local Sponsor of this.

All centres to keep their potential eligible participants informed of the development and to provide a copy of PIS;

Participants will be invited to participate once recruitment resumes

 |

|     | Activity                                             | Pre-COVID Status               | Alternate Arrangements                                                                                                                                                                                                                                                                                                                                                                                                                                                                                                                                                                                                        | Responsibility | Note/Action                                                                                                                                                                                                                                                                                                                                                              |
|-----|------------------------------------------------------|--------------------------------|-------------------------------------------------------------------------------------------------------------------------------------------------------------------------------------------------------------------------------------------------------------------------------------------------------------------------------------------------------------------------------------------------------------------------------------------------------------------------------------------------------------------------------------------------------------------------------------------------------------------------------|----------------|--------------------------------------------------------------------------------------------------------------------------------------------------------------------------------------------------------------------------------------------------------------------------------------------------------------------------------------------------------------------------|
| 1.1 | COVID-19 safety check prior to screening appointment | Not in the current protocol    | 
(1) Screen all potential participants and carers over the phone for cold and flu symptoms, recent overseas or interstate travel and any close contact with a confirmed or suspected COVID-19 case in the past 14-days
 
 
– Individuals with these symptoms should be referred to qualified facilities for further investigation
 
– Individuals with these symptoms requesting advice should be directed to the Health Direct Line [name] or website https://www.healthdirect.gov.au/coronavirus
 
 | All Centres    | 
(1) Personnel to conduct COVID-19 safety check with every call to a participant and delegated Investigators must review any reports of symptoms;
 
(2) Do not see or assess participant on study instruments, or proceed with pathology test, if symptoms present and cause is being investigated. Delay screening appointment until they have been cleared.
 |
| 1.2 | Screening visit conduct                              | Conducted face-to-face on site | 
The options include:
 
 
1) Visiting the trial centre for these assessments where such visits are permitted; COVID-19 safety check and protection measures must be taken
 
2) Verbally consenting to being assessed at a nominated community centre; COVID-19 safety check and protection measures must be taken
 
                                                                                                                                                                                                                                                  | All centres    | The assessors, participant and caregiver will thoroughly wash their hands and/or use hand sanitizer prior to and following a face-to-face visit. Masks and/or gloves to be used in line with local health advice. Centres will need to ensure PPE supplies are readily accessible if conducting face-to-face visits.                                                     |

## 2. SLT001 Trial Contingency Measures for Week 4, 13, and 39 Visits

| .   | Activity                                          | Pre-COVID Status                                                                                          | Alternate Arrangements                                                                                                                                                                                                                                                                                                                                                                                                                        | Responsibility | Note/Action                                                                                                                                                                                                                                                                                                                                                                                                                                                                                                                                                                                                                                                                                                               |
|-----|---------------------------------------------------|-----------------------------------------------------------------------------------------------------------|-----------------------------------------------------------------------------------------------------------------------------------------------------------------------------------------------------------------------------------------------------------------------------------------------------------------------------------------------------------------------------------------------------------------------------------------------|----------------|---------------------------------------------------------------------------------------------------------------------------------------------------------------------------------------------------------------------------------------------------------------------------------------------------------------------------------------------------------------------------------------------------------------------------------------------------------------------------------------------------------------------------------------------------------------------------------------------------------------------------------------------------------------------------------------------------------------------------|
| 2.0 | Week 4, 13, and 39 visits (non-assessment visits) | Face-to-face on site recording of vital signs, adverse events, safety bloods and dispensing IP in Week 13 | 
These visits can be conducted at the trial centre or nominated community centre, through a home visit, or remotely as per Items 2.1–2.5
 
 
Research personnel must screen for COVID-19 symptoms and refer any suspicious case to qualified facilities for further investigation as per Item 2.3
 
COVID-19 safety protection measures must be taken with any face-to-face visits
 
 | All Centres    | 
Items to follow up: vital signs, adverse events and safety pathology tests.
 
Centres will need to assess their current policies and procedures to determine appropriate action for these visits.
 
Researchers to obtain verbal consent to a home visit, or to collect this information over the phone, and record this in the source visit notes.
 
For face-to-face visits: the assessors, participant and caregiver will thoroughly wash their hands and/or use hand sanitizer prior to and following a face-to-face visit. Masks and/or gloves to be used in line with local health advice. Centres will need to ensure PPE supplies are readily accessible if conducting face-to-face visits.
 |

| .   | Activity                        | Pre-COVID Status               | Alternate Arrangements                                                                                                                                                                                                                                                                                                                                                                                                                                                                                                                                                                                                                                                                                                                                | Responsibility | Note/Action                                                                                                                                                                                                                                     |
|-----|---------------------------------|--------------------------------|-------------------------------------------------------------------------------------------------------------------------------------------------------------------------------------------------------------------------------------------------------------------------------------------------------------------------------------------------------------------------------------------------------------------------------------------------------------------------------------------------------------------------------------------------------------------------------------------------------------------------------------------------------------------------------------------------------------------------------------------------------|----------------|-------------------------------------------------------------------------------------------------------------------------------------------------------------------------------------------------------------------------------------------------|
| 2.1 | Vital signs (HR, BP, Ht and Wt) | Recorded during the site visit | 
If unable to do a face-to-face assessment, at the centre or via a home visit, collect this data remotely:
 
 
Wt to be provided by the participant/caregiver over the phone if they have scales at home, otherwise Wt value to be carried forward from previous reading
 
Ht to be carried forward from the previous reading
 
HR and BP to be provided, if possible, by (1) the participant/caregiver if they have a BP facility at home or (2) the study team member or the mobile venipuncturist conducting a home visit. In the latter case, consent needs to be obtained for the team member or venipuncturist to attend home for blood collection and vital sign measurement
 
 | All Centres    | 
Document verbal consent to home visit or remote collection of data, and if opting for mobile venipuncturist, in the source visit notes.
 
If unable to collect data, use last value carried forward method to address missing data.
 |
| 2.2 | Adverse events                  | Recorded during the site visit | Adverse events can be identified and reported over the phone where a face-to-face visit is not feasible                                                                                                                                                                                                                                                                                                                                                                                                                                                                                                                                                                                                                                               | All Centres    | Delegated Investigators need to assess the causality of the reported AEs and SAEs, and to follow up with the participant when needed.                                                                                                           |

| .   | Activity                     | Pre-COVID Status                                                   | Alternate Arrangements                                                                                                                                                                                                                                                                                                                                                                                                                                                                                                                                                                                                                                                                                                                    | Responsibility                             | Note/Action                                                                                                                                                                                                                                                                                                                                                                                     |
|-----|------------------------------|--------------------------------------------------------------------|-------------------------------------------------------------------------------------------------------------------------------------------------------------------------------------------------------------------------------------------------------------------------------------------------------------------------------------------------------------------------------------------------------------------------------------------------------------------------------------------------------------------------------------------------------------------------------------------------------------------------------------------------------------------------------------------------------------------------------------------|--------------------------------------------|-------------------------------------------------------------------------------------------------------------------------------------------------------------------------------------------------------------------------------------------------------------------------------------------------------------------------------------------------------------------------------------------------|
| 2.3 | COVID-19 safety check        | Not applicable                                                     | 
(1) Screen all participants over the phone for cold and flu symptoms, recent overseas or interstate travel and any close contact with a confirmed or suspected COVID-19 case in the past 14-days
 
 
Participants with these symptoms should be referred to qualified facilities for further investigation
 
Participants with these symptoms requesting advice should be directed to the Health Direct Line [name] or website: https://www.healthdirect.gov.au/coronavirus
 
 
(2) If the participant is diagnosed with a coronavirus infection, trial medication may be suspended until symptoms resolve
 | All Centres                                | 
(1) Personnel to conduct COVID-19 safety check with every call to a participant and delegated Investigators must review any reports of symptoms.
 
(2) Do not proceed with pathology test (Item 2.5) if COVID-19 symptoms present and cause is being investigated. Delay appointment until they have been cleared. We will allow deviations in the visit schedule during this time.
 |
| 2.4 | IP dispensing (Week 13 only) | A 3-month supply of IP is dispensed on site by delegated personnel | 
If unable to attend trial centre:
 
A 6-month supply of IP can be delivered by a courier service or through a home visit by a study team member, with visit 5 and visit 6 diaries, and instructions to keep empty packaging/leftover capsules
                                                                                                                                                                                                                                                                                                                                                                                                                                                                                 | All Centres and relevant hospital pharmacy | Obtain verbal consent to receive 6-month IP supply and record this in source notes. Centres will organise courier to deliver IP. Compliance check: Participants will be asked to keep boxes and return them together with unfinished capsules at next visit                                                                                                                                     |

| .   | Activity                                         | Pre-COVID Status                                   | Alternate Arrangements                                                                                                                                                                                                                                                                                                                                                                                                                                                                                                                                                                                                                                                                                                         | Responsibility | Note/Action                                                                                                                                                                                                                                                                                                                             |
|-----|--------------------------------------------------|----------------------------------------------------|--------------------------------------------------------------------------------------------------------------------------------------------------------------------------------------------------------------------------------------------------------------------------------------------------------------------------------------------------------------------------------------------------------------------------------------------------------------------------------------------------------------------------------------------------------------------------------------------------------------------------------------------------------------------------------------------------------------------------------|----------------|-----------------------------------------------------------------------------------------------------------------------------------------------------------------------------------------------------------------------------------------------------------------------------------------------------------------------------------------|
| 2.5 | 2.5.1 Safety Pathology Testing at Weeks 4 and 13 | Conducted at hospital/local pathology laboratories | 
If participant passes the COVID-19 checks, participant will be offered to verbally consent to the following two options:
 
(1) Continue to use the current pathology lab for the testing when on-site visit to pathology lab is permitted
 
(2) Home visit of a qualified study team member or mobile venipuncturist to take blood and deliver to the pathology lab for analysis; infection control procedures will be enacted as per Item 3.1
 
If the participant declines to take either option, the medical history and previous pathology results of the participant will be assessed by the PI in consultation with the coordinating CI to determine if this participant can continue in the trial
 | All Centres    | 
For Option 1, Participant will be provided with a pathology slip; Sponsor to cover the costs of taxi/Uber if needed to avoid public transport.
 
For Option 2, Sponsor to cover the mobile blood collection services if relevant.
 
Centres to record verbal consent to remote blood collection in source visit notes.
 |
|     | 2.5.2 Safety Pathology Testing at Week 39        | Conducted at hospital/local pathology laboratories | To further minimise risk, the Week 39 pathology test can be skipped if there are no abnormal and unresolved findings at Week 26. Otherwise follow 2.5.1 for pathology testing.                                                                                                                                                                                                                                                                                                                                                                                                                                                                                                                                                 | All Centres    | If abnormalities are recorded in the previous tests, Week 39 pathology test will be conducted as per Item 2.5.1                                                                                                                                                                                                                         |

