### **Screening Visit (Week -2 to 0)**

Participants eligible for study recruitment, and their study partner/carer, will have the nature, purpose, and risks of the study explained to them by the investigator. Participants (or person responsible), and their study partner/carer, agreeing to participate in the study will sign the informed consent documents. A unique subject screening number will be issued at the time of consent. The screening visit should occur within 2 weeks prior to randomisation (week 0).

Procedures will be performed in the following order:

- Informed Consent
- Medical history, prior and concurrent medications, and demographics will be documented.
- Body weight and height will be measured.
- Physical examination.
- Blood pressure, pulse rate.
- Neurological Assessment including NINCDS-AIREN diagnostic criteria, NINCDS-ADRDA diagnostic criteria, MMSE, GDS, and check of inclusion and exclusion criteria.
- Blood samples taken and sent to central laboratory for haematology, coagulation, liver function, renal function and electrolytes
- Check concomitant medications and procedures, including any planned hospital admissions.

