### **Week 4 Visit**

- Check concomitant medications and procedures and note any changes in the CRF.
- Vital signs (HR, BP, Ht, Wt) will be measured
- Haematology, coagulation and liver and renal function tests
- Record all AE/SAEs in the CRF
- Record compliance rates

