| 3.1 | VaDAS-cog, Exit-25, CLOX, CIBIS/CIBI C plus  | Conducted face-to-face on site | 
The options include:
 
 
1) Verbally consenting to continuing to visit the trial centre for these assessments at the site where such visits are still permitted; COVID-19 safety check and protection measures must be taken as per Item 3.4
 
2) Verbally consenting to being assessed at a nominated community centre; COVID-19 safety check and protection measures must be taken as per Item 3.4
 
3) Verbally consenting to receive a home visit from assessors; COVID-19 safety check and protection measures must be taken as per Item 3.4
 
 | All centres    | 
For Options 1 & 2, Sponsor to cover the costs of taxi/Uber if needed to avoid public transport.
 
For face-to-face visits: the assessors, participant and caregiver will thoroughly wash their hands and/or use hand sanitizer prior to and following a face-to-face visit. Masks and/or gloves to be used in line with local health advice. Centres will need to ensure PPE supplies are readily accessible if conducting face-to-face visits.
 
If unable to collect data, record as Not Done and explain why in the source notes.
 |

|     |                                         |                                                            |                                                                                                                                                                                                                                                                                                                                                                                                         |                |                                                                                                                                                                                                                                                                            |

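### Appendix 4 item 2.1 carries uncollected vital signs forward, so a filled Week 4 value is a pre-treatment reading shown under an on-treatment visit

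*Protocol*

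**What the plan says.** In the Protocol, section 3.3 and Table 1 schedule vital signs at screening and at Weeks 4, 13, 26, 39 and 52. At screening the list includes "Blood pressure, pulse rate" and "Body weight and height will be measured". The Baseline visit list has no vital signs, and the Week 2 contact is a telephone call for adverse events. At Week 4 the plan is "Vital signs (HR, BP, Ht, Wt) will be measured".

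Appendix 4, part 2, is headed "SLT001 Trial Contingency Measures for Week 4, 13, and 39 Visits". Its item 2.1 applies when vital signs cannot be taken face to face at the centre or at home. For weight, the participant or carer reports a home reading, "otherwise Wt value to be carried forward from previous reading". Height is carried forward. For heart rate and blood pressure the text is "HR and BP to be provided, if possible, by (1) the participant/caregiver if they have a BP facility at home", or by a team member or blood collector visiting the home. The Note/Action column, with all centres responsible, closes with "If unable to collect data, use last value carried forward method to address missing data".

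For the cognitive, executive and global scales at Weeks 0, 26 and 52, item 3.1 uses the same column to say "If unable to collect data, record as Not Done and explain why in the source notes". Item 4.0 gives the same instruction for Week 65.

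Section 5.2 separately names last value carried forward as the way to replace missing data in the intention-to-treat analysis.

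**The concern.** Height apart, nothing in the protocol justifies treating these quantities as constant. A carried-forward reading contributes a change of exactly zero. If the previous reading predates treatment, the entry says nothing about the participant on treatment, although it is filed under an on-treatment visit. Item 2.1 asks for no mark to separate a filled value from a measured one, so a summary by visit could understate any shift in blood pressure, pulse or weight and overstate how many participants were measured. The appendix itself lists vital signs among the things to follow up at these visits, and the trial admits people with stable hypertension, cardiac disease or earlier stroke, so the readings have some safety value.

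**Working it through.** The protocol gives no figure to reproduce here. The check is a trace of the schedule, a comparison of the rules, and one line of arithmetic.

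**Step 1: which reading is carried forward?** (section 3.3, Table 1)

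| Filled visit | Preceding scheduled reading | On treatment? |
|---|---|---|
| Week 4 | Screening (Week -2 to 0) | No, always before treatment |
| Week 13 | Week 4 | Yes if Week 4 was measured; if Week 4 was also filled, the screening value is repeated |
| Week 39 | Week 26 | Yes if Week 26 was measured |

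The pre-treatment problem is therefore certain only at Week 4. A participant for whom Weeks 4 and 13 were both filled would have no measured vital signs between screening and Week 26. That is possible but extreme.

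**Step 2: effect on the mean change at Week 4.** Let f be the share of participants whose Week 4 value is filled. Each filled value has change 0, so

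mean change shown = f x 0 + (1 - f) x (mean change among those measured).

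If filling is independent of true change, the mean among those measured estimates the true mean change, and the result is (1 - f) x true change. The documents give no f, so a range is shown:

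| Assumed f | Share of true mean change shown | For an assumed true shift of 5 mmHg |
|---|---|---|
| 10% | 90% | 0.9 x 5 = 4.5 |
| 20% | 80% | 0.8 x 5 = 4.0 |
| 30% | 70% | 0.7 x 5 = 3.5 |
| 50% | 50% | 0.5 x 5 = 2.5 |

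Under the same independence assumption, the proportion of participants whose change exceeds any fixed non-zero limit shrinks by the same factor.

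**Step 3: the rules side by side.** Item 2.1 covers vital signs at Weeks 4, 13 and 39 and fills the gap. Items 3.1 and 4.0 cover assessments at Weeks 0, 26, 52 and 65 and leave the gap visible. Table 1 has no vital signs at Week 65. No data item at any visit falls under both rules.

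**Step 4: where the filled values would be used.** The safety endpoints in section 1.3 are adverse events and liver, renal and coagulation changes. The Safety Measures in section 5.1 are laboratory tests and adverse events. The three-monthly review in section 5.2 is a tally of adverse events. Vital signs appear in none of these.

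**The case against.** **It may be an analysis rule.** The general sentence in item 2.1 names a method for missing data and resembles the imputation rule in section 5.2, so for heart rate and blood pressure it could point to the analysis rather than to what a site enters. This partly stands. Against it, the sentence sits in the sites' action column beside tasks such as documenting consent, the same column elsewhere says Not Done, and the weight instruction is a carry-forward at collection on any reading. Under the analysis reading the zero change at Week 4 remains, although it could be undone.

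**The case is narrow.** This stands. The appendix applies only during the pandemic, recruitment was paused until centres could resume, and carry-forward comes in only after centre, home and remote collection have failed. Weeks 4 and 13 still require bloods, and a home visitor taking them can also measure pulse and blood pressure.

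**Flagging may be specified elsewhere.** Marking and tabulating filled values commonly sits in the analysis plan or data-management documents, which are not at hand. So it is not established that filled values would pass as measurements, only that item 2.1 does not ask for a mark.

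**Stronger inferences fail.** A reader might infer that items 2.1 and 3.1/4.0 contradict each other; they do not, because they govern different data. A reader might infer that a named safety endpoint or the three-monthly review is diluted; neither is described as using vital signs. Nor does a filled visit necessarily look normal: it repeats the previous reading, whatever that was.

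**Conclusion.** The point holds as a minor one. Item 2.1 directs carry-forward of weight and, on its more natural reading, of any uncollected vital sign. At Week 4 that necessarily places a pre-treatment reading under an on-treatment visit with zero change. The approach is out of step with the Not Done rule elsewhere in the appendix. Only supportive vital-signs data are affected: no named endpoint, efficacy analysis or sample size changes. The loss of (1 - f) rests on an assumed filled share and on filling being unrelated to true change; the 5 mmHg shift is likewise only an illustration.

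**What to change.** In item 2.1, replace the carry-forward instruction for heart rate, blood pressure and weight with the rule already used in items 3.1 and 4.0: record Not Done, with the reason in the source notes. Keep carry-forward for height only. Mark readings reported by the participant or carer from home as such in the eCRF. Summarise vital signs on measured values and give the number measured at each visit. Before lock, ask centres to identify entries already carried forward and set them to missing.

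The cost is an edit to one row of the contingency table and one site query. The downside is more visibly missing vital signs, which is the accurate record.
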